## Abstract

**Background:**

In the past, effortful exercises were considered inappropriate for children with spastic cerebral palsy (CP) due to concern that they would escalate abnormalities including spasticity and abnormal movement patterns. Current scientific evidence indicates that these concerns were unfounded and that therapeutic interventions focused on muscle strengthening can lead to improved functional ability. However, few studies have examined the potential benefits of cardiorespiratory fitness exercises in this patient population.

**Methods/design:**

The rationale and design of a randomized controlled trial examining the effects of a stationary cycling intervention for children with CP are outlined here. Sixty children with spastic diplegic CP between the ages of 7 and 18 years and Gross Motor Function Classification System (GMFCS) levels of I, II, or III will be recruited for this study. Participants will be randomly assigned to either an intervention (cycling) or a control (no cycling) group. The cycling intervention will be divided into strengthening and cardiorespiratory endurance exercise phases. During the strengthening phase, the resistance to lower extremity cycling will be progressively increased using a uniquely designed limb-loaded mechanism. The cardiorespiratory endurance phase will focus on increasing the intensity and duration of cycling. Children will be encouraged to exercise within a target heart rate (HR) range (70 – 80% maximum HR). Thirty sessions will take place over a 10–12 week period. All children will be evaluated before (baseline) and after (follow-up) the intervention period. Primary outcome measures are: knee joint extensor and flexor moments, or torque; the Gross Motor Function Measure (GMFM); the 600 Yard Walk-Run test and the Thirty-Second Walk test (30 sec WT).

**Discussion:**

This paper presents the rationale, design and protocol for Pediatric Endurance and Limb Strengthening (PEDALS); a Phase I randomized controlled trial evaluating the efficacy of a stationary cycling intervention for children with spastic diplegic cerebral palsy.

## Background

Cerebral palsy (CP) is caused by an insult to the developing brain. The prevalence is between 1.5 and 2.5 per 1,000 live births in developed countries [1] and spastic diplegia is the most common form [2]. These children exhibit weakness [3-7] and low endurance [8-12]. Historically, programs to promote physical fitness, including strengthening and cardiorespiratory fitness exercise, were discouraged for patients with spastic CP due to the concern that spasticity and abnormal movement patterns would worsen [13]. Scientific evidence has not supported this concern [14-16] and current research indicates that resistive exercise is an effective intervention to improve strength and function in children with CP [16-21]. However, a recent review of strengthening intervention studies concluded that more research of higher quality is needed [20]. Only one of the studies reviewed was a randomized controlled trial (RCT). The magnitude of the effect size for strength changes varied widely across the studies. Outcome variations may be due to methodological differences in intervention intensity, frequency and duration. There is considerably less research examining the effectiveness of cardiorespiratory fitness for children with CP.

Cycling is a rehabilitation tool often used by physical therapists to improve strength and cardiorespiratory fitness [22] and has been promoted as an appropriate exercise to improve fitness for persons with CP [23,24]. Stationary cycling programs can provide progressive resistance exercise for lower extremity musculature. Normative adult data has demonstrated significant muscle recruitment, based on electromyography (EMG), during cycling for the major lower extremity joint extensors and flexors [25]. Mean recruitment was at least 50% of maximum EMG for the soleus, gastrocnemius, hamstring, vastus medialis/lateralis, rectus femoris and gluteus maximus muscles during the propulsive phase (limb extension) and tibialis anterior muscle during the recovery phase (limb flexion) [25]. Kaplan [26] studied pedaling smoothness and EMG in children with and without CP during a single stationary cycling session. Fifteen children with spastic diplegic CP and 15 nondisabled children were assessed. All children required practice to familiarize themselves with the bike and seven of the children with CP required physical guidance to prevent backward motion at the top of the pedaling cycle. Greater ankle muscle coactivation was observed for all pediatric subjects as compared to that reported for nondisabled adults. Prolonged periods of knee and ankle muscle coactivation occurred in children with CP as compared to controls.

There is limited literature supporting cycling as a therapeutic intervention for children with CP. A tricycle designed to increase hip extensor recruitment in children with CP has been described [27,28] and tested with a small number of children. Five boys with CP between the ages of five and seven years participated in an eight-week home program of tricycle riding. Children cycled an average of 30 minutes per day. Four of the five parents gave the tricycle a high ranking indicating that their children exhibited greater mobility. One study found improved cardiorespiratory fitness, based on a measure of oxygen uptake, in a group of 20 children with spastic and dyskinetic CP following an aerobic exercise intervention that included lower limb cycling [29]. Exercise frequency was three times weekly for 20 minutes. The precise cycling mode and the duration of the exercise, 1.6 – 16 months, varied widely but these results demonstrate that improvement in cardiorespiratory fitness is possible in this population.

Stationary cycling interventions for children with CP warrant further examination as they have the potential to improve strength and cardiorespiratory fitness with minimal requirements for balance and motor control. The purpose of this study is to evaluate the effectiveness of a stationary cycling intervention for children with spastic diplegic CP using a RCT design. We hypothesize that those children randomized to the cycling group will demonstrate a significant improvement in muscle strength, walking endurance, gross motor function and health related quality of life compared to those randomized to the control (no-cycling) group.

## Methods/design

The PEDALS Project for children with CP was designed as a Phase I RCT due to the paucity of previous research that has critically examined the effect of stationary cycling for children with CP. PEDALS is one of four projects hosted by the Physical Therapy Clinical Research Network (PTClinResNet), a member of the Inventory and Evaluation of Clinical Research Networks (IECRN)[30] PTClinResNet was established in 2002 to support research that examines the efficacy of physical therapy interventions. This national network supports evidence-based research across disabilities by linking collaborators across the country representing a range of disciplines, with a coordinating center at the University of Southern California. The organizational infrastructure of PTClinResNet includes a central data management and analysis team, a scientific advisory panel, and a data monitoring and safety board. PTClinResNet uses the International Classification of Functioning (ICF) framework to link outcome measures within and across projects [31,32]. The ICF contains three domains of human function: body function and structure, activity and participation. Body function and structure refers to the physiological function of body systems and the anatomical parts of the body. Activity refers to the performance of a task or action by the whole person. Participation refers to an individual's involvement in life situations. Environmental and personal contextual factors are also included in this framework.

The Institutional Review Boards of the University of Southern California, University of California at Los Angeles, Missouri State University, the State of California, Orthopaedic Hospital in Los Angeles, California and CoxHealth Hospital in Springfield, Missouri granted approvals for this research protocol. This study has a pre-post, control group design with single-blinding. Subjects will be randomly assigned to intervention versus control groups. There are two stratifying variables; age (younger, 7–11 and older, 12–18 years) and selective voluntary motor control ability (good versus fair). Randomization to the intervention or control group will be blocked by these two variables. The assessment of selective motor control ability for children with CP has been described by Staudt and Peacock [33]. Good selective motor control is defined as the ability to isolate knee and ankle movement out of synergy (knee extension with the hip in flexion and ankle dorsiflexion with the knee in extension). Fair selective motor control is defined as the ability to isolate knee movement without obligatory hip movement. Only subjects who demonstrate good selective motor control bilaterally will be placed in the good selective motor control category for stratification. Subjects who have poor selective motor control (cannot isolate knee and ankle joint motion out of synergy) bilaterally will be excluded from the study. All others will be placed in the fair selective motor control category.

Interventions will be performed by physical therapists in community clinics throughout Southern California and Southwest Missouri. Evaluations will take place at the University of Southern California or Missouri State University and will be performed by physical therapists blinded to subject group randomization. Evaluation and intervention physical therapists will attend instructional sessions and receive a written manual of procedures specific to either evaluation or intervention protocols. Performance will be videotaped during mock sessions and scored by members of a standards committee using a checklist of critical components for each protocol. To participate in the study, therapists must achieve a minimum score of 90% accuracy. In addition, they will be provided with feedback for aspects of the protocol that are not performed optimally.

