### Subjects

Subjects will have a diagnosis of spastic diplegic CP. Inclusion criteria will be: 1) age between 7 and 18 years; 2) ability to follow simple verbal directions; 3) good or fair selective motor control for at least one lower limb and 4) ability to walk independently indoors, with or without assistive devices (Levels I-III of the Gross Motor Function Classification System (GMFCS) [34]. Exclusion criteria will be: 1) orthopedic surgery, neurological surgery or baclofen pump implantation within the preceding 12 months; 2) botulinum toxin injections within the preceding three months; 3) serial casting or new orthotics within the preceding three months; 4) initiating oral medications that affect the neuromuscular system, e.g. baclofen, within the preceding three months; 5) onset of physical therapy, exercise, sport activity or change in assistive devices for walking within the preceding three months; 6) inability or unwillingness to maintain age appropriate behavior; 7) serious medical conditions such as cardiac disease, diabetes or uncontrolled seizures; 8) current participation in a fitness program that includes cardiorespiratory endurance exercise, at least one time per week and 9) significant hip, knee or ankle joint contractures preventing passive movement of the lower limbs through the pedaling cycle.

Subjects will be recruited from southern California and southwest Missouri via flyers and brochures placed in clinics and schools and by postings on disability related web sites. When a potential subject contacts the investigators, a telephone screening will be performed. Subjects meeting the inclusion and exclusion criteria assessed during the telephone screening will receive an in-person screening to determine GMFCS level and selective motor control ability. Additionally, the child will be assessed on the stationary bicycle to ensure that their lower extremity joint range of motion is sufficient to move through the pedaling cycle.

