If the subject qualifies during the in-person screening, enrollment procedures will occur. An investigator will explain the informed consent, medical release, photo consent and a summary of the Health Insurance Portability and Accountability Act of 1996 (HIPAA) policy to the participants and their guardians. Testing purposes and procedures, the randomization process, potential risks and benefits for participants and responsibilities of both the participants and the research team will be discussed and questions answered. If the individual and their parent/guardian decide to proceed with enrollment, the consent form will be signed and an enrollment form, containing the subject's age and selective motor control ability, will be submitted to the PTClinResNet Data Management Center for subject randomization. Families will be notified of their child's assignment to the control or intervention group following the baseline evaluation.

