#### Outcome data measurements

Outcome measures for this study include assessments at the body function and structure, activity and participation levels of the ICF. Primary outcome measures are: 1) knee joint extensor and flexor torque; 2) the Gross Motor Function Measure (GMFM) Sections D: Standing and E: Walking, Running and Jumping [38]; 3) the 600 Yard Walk-Run test [39] and 4) the Thirty-Second Walk test (30 sec WT) [40]. Secondary measures are: 1) the Pediatric Outcomes Data Collection Instrument (PODCI) [41], 2) the Pediatric Quality of Life Inventory™ (PedsQL) [42-44] and 3) instrumented gait analysis.

Knee joint extensor and flexor moments, commonly referred to as joint torque in a clinical setting, are measures at the body function and structure level of the ICF. A Kin-Com dynamometer (Chattanooga Group Inc., Hixson, TN) will be used for data collection at the Los Angeles site and a Biodex Multijoint System (Biodex Medical Systems Inc., Shirley, NY) at the Missouri site. The subject will be seated with the trunk slightly reclined. Straps at the waist, chest, thigh and distal aspect of lower leg will be used to secure the subject to the testing device. The axis of the device's moving arm will be aligned with the subject's knee joint center. The subject will be directed to observe the computer screen for visual feedback while being verbally encouraged by the investigator to provide maximum effort. Five repetitions of knee joint extension and flexion at 0, 30, 60 and 120 degrees/second will be performed bilaterally. The peak joint moment for each group of five contractions will be determined.

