The GMFM assesses performance at the activity level of the ICF. It has been shown to be valid [45] and reliable [46] for assessing children with CP. Two of the five dimensions, Dimension D: Standing (13 items) and Dimension E: Walking, running, and jumping (24 items) will be tested. GMFM sessions will be videotaped to permit review should a question about a particular score arise. Subjects will wear shorts and be tested barefoot and without assistive devices or ankle-foot orthoses. The evaluation therapists will follow the procedures outlined in the Gross Motor Function Measure User's Manual [38] for testing and scoring. Each item will be scored as 0 = does not initiate, 1 = initiates, 2 = partially completes, 3 = completes or NT = not tested. The data will be analyzed using the GMFM-66 Ability Estimator Software. The advantage of the software is the conversion of the ordinal data into an interval scale. This will allow for a more accurate estimate of the child's ability and provide a measure that is equally responsive to change across the spectrum of ability levels [38].

The 600 yard walk-run test [39] assesses walking and/or running endurance at the activity level of the ICF. This test is an indirect measure of cardiorespiratory fitness and is reflective of a child's ability to participate in play and sport activities. It is a standardized physical fitness test developed for school-age children. Fernhall et al. [39] used this test for children with intellectual disabilities and found a high correlation with laboratory measures of peak V0_2_. During this test, children are asked to complete a 600 yard distance as fast as possible by running, walking or a combination of both. The distance required will be clearly explained so they may pace themselves. Orange cones will be placed to visibly mark the perimeter of the circular path. Subjects will be encouraged verbally to continue walking or running until they complete the 600 yard distance. If a subject cannot complete this distance within 15 minutes or stops for more than five seconds, the test will be stopped. At the end of the test, the distance completed and the time will be recorded. Distances of less than 600 yards will be measured using a distance-measuring wheel. Outcomes include the distance the child is able to complete, the time for completion and the speed.

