### Data analyses

Student t-tests (if normally distributed) or Wilcoxon rank sum tests (if non-normal) will be used to contrast the change from baseline within and between the intervention and control groups for the primary hypotheses. Analysis of covariance procedures will be used to contrast changes adjusting for selective voluntary motor control (good versus fair) and age group (younger, 7–11 years) and (older, 12 – 18 years) for primary outcome measures.

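### GMFCS level is determined at screening but is not a named ANCOVA covariate; adding it would be a cheap, minor gain in precision for the three walking and gross motor outcomes

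*Protocol article*

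**What the plan says.** All from the protocol article.

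- **Eligibility (Subjects).** Children qualify with "ability to walk independently indoors, with or without assistive devices (Levels I-III of the Gross Motor Function Classification System (GMFCS"), so the sample can run from unaided walkers to children who use devices.
- **Screening (Subjects).** Candidates who pass the telephone screen "will receive an in-person screening to determine GMFCS level and selective motor control ability". GMFCS level is therefore known before allocation.
- **Randomization (Methods/design and Subjects).** "There are two stratifying variables; age (younger, 7–11 and older, 12–18 years) and selective voluntary motor control ability (good versus fair"). The enrollment form is described as "containing the subject's age and selective motor control ability, will be submitted to the PTClinResNet Data Management Center for subject randomization".
- **Outcomes (Outcome data measurements).** "Primary outcome measures are: 1) knee joint extensor and flexor torque; 2) the Gross Motor Function Measure (GMFM) Sections D: Standing and E"; the other two are the 600 Yard Walk-Run and the 30-second walk. All except knee torque are placed at the activity level of the ICF.
- **Analysis (Data analyses).** t-tests or rank sum tests "will be used to contrast the change from baseline within and between the intervention and control groups for the primary hypotheses". Then: "Analysis of covariance procedures will be used to contrast changes adjusting for selective voluntary motor control (good versus fair) and age group". GMFCS is not mentioned there.

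**The concern.** Three of the four primary outcomes measure standing, walking or running, and GMFCS grades gross motor function. It is natural to expect it to be prognostic for these outcomes, although the article gives no correlation with either their level or their change. The two factors that are used are age group and selective motor control. The latter is rated from isolated knee and ankle movement, and the article does not say how closely it follows walking ability.

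If change over the 10 to 12 weeks depends on GMFCS level, two things follow. Variation between levels stays in the residual and lowers power. And an allocation that happens to put more level III children in one arm moves the estimate for that trial.

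The 600-yard test is where such dependence is most plausible. Distance cannot exceed 600 yards, and the test ends at 15 minutes or once a child has stopped for more than five seconds. A child who finishes at baseline cannot gain distance. A child who does not finish has no 600-yard completion time to improve. Speed, the third outcome of that test, is less constrained. For the 30-second walk the article describes no such limit, so dependence there is only an assumption.

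**Working it through.** **1. The plan's own figure.** Sample size states 80% power with 30 per group, effect 0.7, two-sided 0.05, two-group t-test. The noncentral t calculation gives 76.0% (normal approximation 77.4%). The gap from 80% is a separate matter and does not support this point; 76% is simply the starting value in step 5.

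**2. How often the arms differ.** The article does not give the share of level III children, so I assume 12, 20 or 30 of 60. With 30/30 allocation made without regard to level, the number X of level III children in one arm is hypergeometric (60 children, K at level III, 30 drawn), and the difference between arms is |2X − K|.

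| Level III of 60 (assumed) | P(difference ≥ 4) | P(difference ≥ 6) | P(difference ≥ 8) |
|---|---|---|---|
| 12 | 33% | 10% | 2% |
| 20 | 41% | 17% | 5% |
| 30 | 44% | 20% | 7% |

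**3. What a difference does to the planned comparison.** Let g be the difference in mean *change* between level III and levels I–II, in SD of change (assumed 0.25, 0.5 or 0.8). An excess of d children shifts the comparison by (d/30) × g. For d = 6:

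- g = 0.25: 0.2 × 0.25 = 0.05 SD
- g = 0.5: 0.2 × 0.5 = 0.10 SD
- g = 0.8: 0.2 × 0.8 = 0.16 SD
- g = 0: no shift

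The standard error of the comparison is √(2/30) = 0.26 SD. Dividing the shifts by it gives 0.19, 0.39 and 0.62. The chance of a false positive *given* that imbalance, Φ(−1.96 + z) + Φ(−1.96 − z), is then 5.4%, 6.7% and 9.5%.

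**4. Level versus change, by simulation.** 8,000 trials per scenario, one third of children at level III on average, level III 2 SD lower at baseline, no treatment effect. The mean shifts are for trials with an excess of six or more level III children in the cycling arm.

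| Scenario | Shift in post-test score | Shift in change | Shift in change after adjusting for level III | Type I error for change, all trials |
|---|---|---|---|---|
| Change unrelated to level | −0.47 | 0.00 | 0.00 | 5.0% |
| Change 0.5 SD lower at level III | −0.60 | −0.12 | 0.00 | 4.8% |

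The change score removes the baseline gap. Only dependence of change on level gets through, and the covariate removes it.

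**5. Precision.** If GMFCS explains a fraction R² of the residual variance of change (assumed), the effective effect size is 0.7/√(1 − R²). With 30 per arm, t-test power is:

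- R² = 0: 76%
- R² = 0.05: 78%
- R² = 0.10: 80%
- R² = 0.20: 85%

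These values use 58 degrees of freedom. Deducting 2 for the covariate lowers each by about 0.05 percentage points (for example 75.99% to 75.94%).

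**The case against.** The case against is strong on several counts.

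- **Uncorrected imbalance.** A reader might infer that a chance excess of device users leaves the comparison uncorrected. It does not: the planned comparison is of change from baseline, which removes a pure difference in level (step 4). This objection stands.
- **Bias.** A reader might infer that the trial is biased. Chance imbalance is what randomization and the test already allow for, and type I error over all allocations stays at about 5%. This stands.
- **GMFM floor and ceiling.** The GMFM is done with "Subjects will wear shorts and be tested barefoot and without assistive devices or ankle-foot orthoses", so a reader might infer that level III children sit near the floor and level I near the top. The article does not document those positions. It also plans GMFM-66 scoring, chosen partly so that the scale responds to change to the same degree at all ability levels. The argument should not be used.
- **Availability of GMFCS.** The enrollment-form sentence describes what is sent for randomization. It does not say that GMFCS is unavailable for analysis.
- **Design choice.** Two stratifiers for 60 children, with adjustment for both, is defensible. Selective motor control may also carry part of what GMFCS would add, so the relevant R² is what GMFCS explains beyond the two named covariates.
- **Condensed article.** A separate analysis plan may name further covariates. That is possible, but this article does list its covariates, and GMFCS is not among them.

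What is left is precision, and protection in an unlucky allocation, where change depends on level.

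**Conclusion.** The point holds as a minor one. A variable known before allocation, and directly relevant to three of the four primary outcomes, is not among the covariates the article names. This is neither an error nor a contradiction, and the stratification is not at fault.

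Its size rests on assumptions, because the article gives neither the level III share nor any relation between GMFCS and change. With 12 to 30 level III children among 60, a difference of six or more between arms has a probability of 10% to 20%. Such a gap of exactly six moves the estimate by 0.05 to 0.16 SD if mean change differs by 0.25 to 0.8 SD, against a design effect of 0.7. The potential power gain is about 2 to 9 percentage points (76% to 78–85%) for R² of 5% to 20%. If change does not depend on GMFCS, both are essentially zero.

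**What to change.** Keep the two stratifiers. Adding three GMFCS levels would give 2 × 2 × 3 = 12 cells, about 5 children each, which is too sparse.

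Under Data analyses, prespecify GMFCS level (I, II, III), taken from the in-person screening record, as an additional ANCOVA covariate for the GMFM, 600-yard and 30-second walk outcomes, alongside age group and selective motor control. Fix this before outcome data are seen by arm, and carry the screening value into the analysis data set.

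The cost is 2 degrees of freedom per model and one data field that is already determined at screening. The downside is little or no gain if change proves unrelated to GMFCS.
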